### Assignment of intervention and blinding

2.3

A stratified randomization process will be performed by the external research, considering the H&Y stages. Because patient recruitment will occur over a prolonged period, to control the stratification, the randomization will be performed after 12 participants group recruitment, and this process will be repeated six times, with the exception that the last group of recruitment will be of 14 people instead of 12. The allocation in each group of recruitment will be 1:1, using a function of Microsoft Excel (V18.0, 2021. Excel; Microsoft Corp). To ensure masking, the raters physiotherapist, and data analysis researcher, will be blinded to the participant’s allocation. Although participants and treating physiotherapists cannot be totally blinded to the intervention performed, the hypothesis and objectives of the study will be hidden from them. At the same time, all participants will be instructed not to disclose information regarding their intervention to the raters’ physiotherapists. To control expectancy effects, it will be explained to patients that it is not yet determined which therapy is more effective. On the other hand, a consecutive number code will be assigned to the participants without disclosing the treatment group to which they belong.

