**Methods:**

The GAITimagery is designed as a double-blind, randomized control trial, including a convenience sample in 2 parallel groups (1:1) with two interventions of 2 sessions per week during 6-week and 8-week follow-up. The initial recruitment will be 88 participants with idiopathic PD and unimpaired cognition state, who will be randomly divided into two groups: GAITimagery (GiG) or the active control Gait group (GaG). Both will perform the same gait exercises but only GiG will include MI training. Gait speed is the primary outcome, while Maximum gait speed (m/s) and Gait speed variability are the secondary results. The tertiary outcomes are related to Quality of life, Daily life activities, Freezing of gait, Balance, Mobility, and Gait performance measures to psychometrics and biomechanics instruments. All results will be measured at baseline (t0), post-training (t1), and follow-up assessment (t2) 8 weeks after finished physiotherapy programs.

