#### Intervention

2.2.2

Two physiotherapy programs, GAITimagery and gait physiotherapy program, have been scheduled to take place over 6-week period. Each program involves two non-consecutive sessions per week, lasting 60 min each, which makes a total of 12 sessions. Additionally, this study proposes an 8-week follow-up period, which extends beyond the intervention phase. The rationale for this design is based on evidence that the benefits of gait exercises for PD emerge rapidly and are sustained over time, achieving short-term improvements in 12 to 14 training sessions over 2 to 4 weeks (27), which can persist for 3 to 12 months after treatment completion (30). The GAITimagery program will be performed for the GiG, while the GaG will develop the gait physiotherapy program without the MI exercises. To replicate the same conditions in both programs, the sessions will be done in groups of two people with the same PD severity according to the Hoehn & Yahr (H&Y) scale. Each program will be developed by different physiotherapists with an assistant, and supervised by a third physical therapist who checks that the walking exercises applied in both groups are the same. The sessions of both programs also have the same structure: warm-up (10′), central phase (45′), and cool-down (5′). Both interventions will be performed in a quiet environment, in a 7x13m room located in an area isolated from outside noise to promote the concentration of participants during the sessions. The warm-up and cool-down are the same in both programs. The essential aspects of physiotherapy in PD will be included in the warm-up section, related to respiratory exercises, dissociation of the shoulder and pelvic girdle, transfers and postural changes, joint mobility, balance, and strengthening (31). The cool-down part cover self-assisted stretching.

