#### Sample size and recruitment

2.2.4

Sample size calculation has been done with the G*Power software (Universität Kiel, Germany, Version 3.1) (59), based on the expected differences in gait performance between experimental and control groups. Due to the absence of statistical differences between groups in the previous works that compare gait physiotherapy with and without MI, the estimation was settled with a small expected size effect of *F* = 0.15 (60). A power of 80% and a type I statistical error of 5% were considered in a mixed factorial design (2 groups and 3 times assessments), which resulted in 74 participants as the total sample size. Considering 20% of drop-outs, the recruitment will be 44 people per group. For the participant’s recruitment, the research coordinator of the study will establish communication with local health centers to provide information and contact details about the GAITimagery study. The centers will be asked to distribute this information among potential participants through brochures, after which those interested in participating will have to communicate their intention by telephone to the coordinator research. After this, an appointment to evaluate the participation criteria and the severity of the disease will be given to the people who have established communication with the study. The recruitment process will remain open until the necessary number of people is met according to the sample size calculation, as long as it does not exceed 2 years. If this time ends, the preliminary results will be reported, informing the power of the study fulfilled with the sample obtained.

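### The randomisation schedule sums to 74 people (86 at most), not the 88 the plan recruits, and its last group of 14 gives an odd number per arm.

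*Protocol article*

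**What the plan says.** Four statements in the protocol article bear on this.

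- **Abstract, Methods:** "The initial recruitment will be 88 participants with idiopathic PD". These are the people to be divided at random between the two arms.
- **Section 2.2.4 (Sample size and recruitment):** the calculation, for a 2-group, 3-time mixed design, is one "which resulted in 74 participants as the total sample size". Then: "Considering 20% of drop-outs, the recruitment will be 44 people per group", that is 88 in all.
- **Section 2.3 (Assignment of intervention and blinding):** randomisation is stratified by Hoehn & Yahr (H&Y) stage, is run externally, and is done each time a group of 12 has been recruited. The section adds that "this process will be repeated six times, with the exception that the last group of recruitment will be of 14 people instead of 12". Allocation is 1:1 within each recruitment group.
- **Section 2.2.2 (Intervention):** in both programmes "the sessions will be done in groups of two people with the same PD severity", as measured by H&Y.

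**The concern.** The allocation schedule is an operational figure: the external researcher will build the list from it. It should cover everyone who is recruited, and it does not. Its natural total is the pre-drop-out sample, which suggests that the drop-out allowance was added to the recruitment target but never carried into section 2.3.

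A list built from that section would run out before recruitment does. Allocation would then either stop early, with no allowance for loss, or continue under a rule that the protocol has not written down. The introduction names non-stratified randomisation as a weakness of earlier trials, so the allocation procedure is part of this trial's own rationale.

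The last group of 14 raises a smaller, practical point, because both programmes treat people in twos.

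**Working it through.** **1. The plan's own sample size.** Inputs from section 2.2.4: a "small expected size effect of *F* = 0.15", power 80%, two-sided type I error 5% (F test), k = 2 groups, m = 3 times. The article gives neither the correlation between repeated measures (ρ) nor a sphericity correction. I assume ρ = 0.5 and sphericity. For the group-by-time interaction:

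- noncentrality λ = f² × N × m / (1 − ρ)
- df1 = (k − 1)(m − 1) = 2
- df2 = (N − k)(m − 1)

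At N = 74, λ = 0.0225 × 74 × 3 / 0.5 = 9.99 and df2 = 144, giving power 0.806. At N = 72 power is 0.795. So 74 is the smallest even total that reaches 80%, and the stated figure is reproduced. With ρ = 0.3 the required N would be 102, and with ρ = 0.7 it would be 46.

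**2. The recruitment target.** 74 / 2 = 37 per arm; 37 × 1.2 = 44.4, stated as 44; 2 × 44 = 88.

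**3. The schedule total.**

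| Reading of section 2.3 | Sum | Total | Short of 88 by |
|---|---|---|---|
| Six groups, the last of 14 | 5 × 12 + 14 | 74 | 14 (16%) |
| One run plus six repeats, the last of 14 | 6 × 12 + 14 | 86 | 2 |

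Neither gives 88.

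**4. Effect on power.** Apply the plan's 20% loss to each total, rounding down, with the formula in step 1 and ρ = 0.5:

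| Randomised | Completers | λ | df2 | Power |
|---|---|---|---|---|
| 88 | 70 (70.4) | 9.45 | 136 | 0.782 |
| 86 | 68 (68.8) | 9.18 | 132 | 0.769 |
| 74 | 59 (59.2) | 7.97 | 114 | 0.703 |

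Stopping at 74 rather than 88 costs 0.782 − 0.703 = 0.08. Stopping at 86 costs about 0.01. Over a range of assumed correlations, 70 against 59 completers gives 0.628 against 0.548 at ρ = 0.3 (a loss of 0.08), and 0.950 against 0.906 at ρ = 0.7 (a loss of 0.04).

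**5. Pairs.**

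- A group of 12 at 1:1 gives 6 per arm, which is three pairs.
- A group of 14 gives 7 per arm: three pairs and one person over in each arm.
- A total of 74 gives 37 per arm, also odd, so on that reading one person per arm is left over even when pairs are formed across groups.
- A total of 86 gives 43 per arm, odd as well.
- A total of 88 gives 44 per arm, or 22 pairs by number.

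Whether pairs share an H&Y stage depends on the stage mix, which the article does not give.

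**The case against.** The case for leaving the text alone is that the schedule sentence is not a stopping rule. Section 2.2.4 keeps recruitment open, for up to two years, until the number from the sample-size calculation is reached. If the list ran out, the obvious course would be to run another group by the same procedure. On the 86 reading only two people are at issue. This stands as far as consequences go: nothing says that the trial will stop at 74, or that later participants would be allocated outside the external, stratified procedure. It does not remove the mismatch, because no statement in the article makes the schedule sum to 88.

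Three stronger readings are tempting and are not supported.

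- **The batch sizes make same-stage pairs impossible.** This would need partners to come from one recruitment group and exact 1:1 balance within every stage in every group. The article states neither. Groups of 12 can yield three pairs per arm. Any probability that they fail would rest on an invented stage mix.
- **Power drops from 0.81 to 0.70.** That sets 74 completers against 59. The plan as written randomises 88 and expects about 70 to complete, so the fair starting point is 0.78. (It lies below 0.80 because the allowance multiplies by 1.2 instead of dividing by 0.8, which is a separate matter.)
- **Re-pairing would undo the stratification.** Session partners are arranged after allocation. Changing them alters neither arm membership nor the H&Y balance between arms.

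**Conclusion.** The numerical contradiction holds. Section 2.3 allocates 74 people on the natural reading and 86 on the most generous one, while the abstract and section 2.2.4 recruit 88. The exact match with 74 makes a missed drop-out allowance the likely cause, though the article does not say so.

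If the schedule were followed to 74, power would be about 0.70 against about 0.78. That rests on the 20% loss in the plan, an interaction test and an assumed ρ of 0.5; the loss is 4 to 8 percentage points for ρ from 0.7 to 0.3. On the 86 reading the effect on power is negligible.

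The pairing point is narrower. The group of 14 leaves one person per arm without a partner within that group, and nothing in the batch rule ensures partners of the same stage. Matching across groups is not ruled out, so this calls for a clarification and does not show the design to be unworkable.

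**What to change.** Before the first allocation, reconcile the abstract, section 2.2.2, section 2.2.4 and section 2.3:

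1. Restate the schedule so that it sums to 88 with an even number per arm in every group. One example is six groups of 12 and a last group of 16: 6 × 12 + 16 = 88, with 6 per arm in each group of 12 and 8 per arm in the last. Keep the external, H&Y-stratified 1:1 procedure as it is.
2. State that session partners may be matched across recruitment groups within an arm. Even arm sizes alone do not guarantee partners of the same stage.

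The cost is a few sentences in section 2.3, one in section 2.2.2, and an allocation list built to the new total. It adds no participants beyond the 88 already planned. The article expects recruitment from September 2025. Made before then, this is a correction on paper; made after groups have been allocated, it would change the randomisation procedure mid-trial.

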### Data collection, management data, and statistical analysis

2.4

An electronic template was prepared with the items from the clinical interview and results from scales and questionnaires, to ensure no missing data. All the assessments will be registered under a code assigned to each participant (coding). In this way, the data dump to a database is carried out under the supervision of one of the evaluators who, in turn, has the task of guaranteeing anonymization of the participants in the outcomes registry. Personal participants’ data from the clinical interview will be located separately from the main dataset on a local computer to protect confidentiality during all trial phases. The raw dataset will be maintained for 10 years after the completion of the trial with indefinite restricted access due to sensitive data. No individual data from participants will be openly available. Instead, all additional information to the results presented in future publications will be provided through the corresponding supplementary material to each publication. Lastly, the participants do not receive any incentives or compensation for participation in this study.

Statistical analyses will be performed using SPSS v.24 (SPSS Inc., Chicago, IL, USA). If adherence issues occur, all analyses will be evaluated using intention-to-treat principles, with a level of significance of 0.05. Mean and standard deviations (SD) will be calculated to inform all the continuous variables that have a normal distribution. On the contrary, continuous outcomes with an asymmetric distribution will be reported through the median. Outcomes from ground reaction forces will be standardized based on the weight of participants. Categorical results will be informed through frequency. To check for differences between groups on the demographic outcomes, multivariate one-way analysis with the between-subject factor *Group* will be conducted. Furthermore, to test for sex differences between groups, a chi-square test will be used.

A two-factor mixed Multivariate Analysis of Variance (MANOVA) will be conducted to analyze the factors effects on the outcomes registered at t0, t1, and t2. The within-subject factor is *Time* with three categories (Baseline, Postintervention and Follow-up). The between-subject factor is *Group* with two categories (GiG and GaG). When significant effects are found, Bonferroni will be used for post-hoc comparisons. Differences shall be declared statistically significant if *p* < 0.05. Before the referred statistical analysis above, the following assumptions will be checked: (1) Normality: the distributions of the residuals will be tested using the Shapiro–wilk test; (2) Sphericity: the homogeneity between variances of the differences between pairs of measures will be checked with the Mauchly sphericity test; (3) Homoscedasticity: homogeneity of variances will be evaluated using the Levene test; (4) Equality of covariance matrices: the equality of variance–covariance matrices across the cells formed by the between-subjects effects will be tested with the Box’s *M* test; (5) Absence of multicollinearity, the correlation level between dependent variables will be observed with the Pearson correlation test. If any of these assumptions are not met, the necessary statistical corrections will be used (61).

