#### Setting and eligibility criteria

2.2.1

Participants will be recruited from the local hospitals and rehabilitation centers of the city of Valencia. The eligibility criteria assessment, obtaining informed consent (Supplementary material 3), assessments, and intervention of both groups will be carried out in the facilities of the Physiotherapy Department at the University of Valencia. The recruitment and eligibility criteria assessments will be accomplished by a neurologist from the hospitals who regularly carry out pharmacological and disease supervision. The inclusion criteria are: (1) diagnosed with PD according to the United Kingdom Parkinson’s Disease Society Brain Bank diagnostic scale; (2) independent walk in a 10-meter corridor; (3) normal cognitive state, determined by the Mini-Mental State Examination with a score ≥ 25 and the Montreal Cognitive Assessment ≥26; and (4) stable medication from the month prior to the start of the study until the t2 assessment. Likewise, the exclusion criteria are: (1) additional neurological condition different from PD; (2) disease or musculoskeletal acute alteration that limits mobility or balance; (3) lower extremities asymmetries >1 cm; (4) report pain on the Visual Analog Scale; (5) suffer from blindness, deafness or any other visual/hearing impairment or pathology that may influence the ability to understand instructions and carry them out; (6) significant tremor that may interrupt the MI exercise; and (7) to perform other physical therapies or sports during the trial or in the 2 months before.

We expect patient recruitment to begin in September 2025 and completed in July 2026. All patients are assumed to have completed baseline testing in September 2026. In addition, the recruitment of healthy people counterparts will be carried out once the participation of patients with PD ends, to recruit people with similar characteristics of age, weight, height, and gender. This procedure will be carried out at the local city’s Municipal Senior Activity Center. The inclusion and exclusion criteria are the same for patients, except those related to the PD.

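### Intention-to-treat depends on undefined adherence issues, and the three-visit MANOVA may drop participants who have a valid gait speed at t1, the primary time point

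*Protocol article*

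**What the plan says.** All references are to the protocol article.

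- **Analysis population (section 2.4).** "If adherence issues occur, all analyses will be evaluated using intention-to-treat principles, with a level of significance of 0.05". Adherence issues are not defined, and no analysis set is named for the case where none are judged to have occurred.
- **Method and software (section 2.4).** "Statistical analyses will be performed using SPSS v.24", and "A two-factor mixed Multivariate Analysis of Variance (MANOVA) will be conducted to analyze the factors effects on the outcomes registered at t0, t1, and t2". Time has three levels and Group has two.
- **Missing data (section 2.4).** The only provision is preventive: an electronic template for the clinical interview and "results from scales and questionnaires, to ensure no missing data". It does not cover gait speed from the dynamometric platform, and it cannot prevent a missed visit.
- **Expected loss (section 2.2.4).** "Considering 20% of drop-outs", 44 people per group are to be recruited, against a calculated total of 74.
- **Primary endpoint (section 2.2.3).** Gait speed at t1. The t2 visit is not the primary time point.
- **Criteria that run past randomisation (section 2.2.1).** Inclusion criterion 4 asks for "stable medication from the month prior to the start of the study until the t2 assessment". Exclusion criterion 7 is "to perform other physical therapies or sports during the trial or in the 2 months before".
- **Monitoring (section 2.5).** Weekly calls record medication changes and outside physical activity, among other things. An internal committee may end a person's participation on the strength of these reports. The same calls are meant to support retention.

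**The concern.** Intention-to-treat protects the randomised comparison only if it is fixed in advance. Here it takes effect on a judgement about conduct during the trial, so the analysed population could be settled once conduct is known.

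The condition also looks at the wrong event. Adherence concerns the sessions, whereas the MANOVA loses people through missed assessments. Someone who attends all 12 sessions and then misses t2 has no adherence issue, yet has an incomplete record. A repeated-measures MANOVA in SPSS works on complete records, so unless values are imputed first that person leaves the t1 comparison for lack of a later, non-primary visit.

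The running eligibility criteria and the committee's power to end participation are a further possible source of incomplete records. Section 2.3 concedes that participants cannot be fully blinded. Medication change, outside exercise and withdrawal could therefore plausibly relate to arm or to response. At stake are the validity of the primary comparison and the truth of the intention-to-treat claim.

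**Working it through.** **Inputs from the article:** f = 0.15, two groups, three assessments, alpha 0.05, power 80%, total 74, drop-out 20%, 44 per group (88 in all).

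**Assumed, because not stated:** correlation between visits rho = 0.5, no sphericity correction, half of those lost by t2 still seen at t1.

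**1. The plan's own figure.** For the group-by-time interaction in a repeated-measures ANOVA, lambda = f² × N × m / (1 − rho), with df1 = (k − 1)(m − 1) = 2 and df2 = (N − k)(m − 1).

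- N = 74: lambda = 0.0225 × 74 × 3 / 0.5 = 9.99, df2 = 144, power 80.6%.
- N = 72: power 79.5%.

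The stated 74 is reproduced at rho = 0.5.

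**2. Records left for the MANOVA.**

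- Complete at all three visits: 88 × 0.80 = 70.4, about 70.
- Seen at t1, under the assumption above: 88 × 0.90 = 79.2, about 79.
- Measured at the primary time point but deleted: 79.2 − 70.4 = 8.8, about 9 people.
- Variance ratio for the t1 contrast: 79.2 / 70.4 = 1.125, about 12% larger.

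If none of those lost were seen at t1, the ratio would be 1. If all of them were, it would be 88 / 70.4 = 1.25.

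**3. Power.** At N = 70, lambda = 0.0225 × 70 × 3 / 0.5 = 9.45 and df2 = 136, which gives 78.2%.

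| rho | power at N = 74 | power at N = 70 |
|---|---|---|
| 0.3 | 65.5% | 62.8% |
| 0.5 | 80.6% | 78.2% |
| 0.7 | 96.0% | 95.0% |

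The move from 74 to 70 costs 1 to 3 points. At rho = 0.5, 30% loss instead of 20% would give 72.7%. These figures are for the interaction test that was sized, not for a t1 contrast.

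**4. Bias (illustration).** Suppose a fraction p is deleted in each arm, and the deleted-minus-retained difference is g SD larger in one arm than in the other. The group difference then shifts by p × g.

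- All loss, p = 0.20: g from 0.25 to 1.0 gives 0.05 to 0.20 SD.
- Only those measured at t1 and then deleted, p = 8.8 / 79.2 = 0.11: the same g gives about 0.03 to 0.11 SD.

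The second range is the part that can be avoided simply by keeping data already collected. The article gives no value for g.

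**The case against.** **With full adherence, intention-to-treat and per-protocol coincide, so the conditional sentence may do no harm.** This is fair as far as treatment departures go, and the sentence does cover all analyses and names no rival per-protocol set. But the trigger is undefined, and missed visits by people who adhered fall outside it. A later analysis plan could define terms, but it could not make the rule unconditional without contradicting this sentence.

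**Complete-case analysis is nowhere stated.** Correct. It is a property of the named method. Imputation before the MANOVA is not excluded and may sit in an analysis plan that is not shown. For that reason the point is worded as people who may be lost. What stands is that the article plans 20% drop-out and fixes a method that does not by itself use incomplete records, when a better one is available in the same software.

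**A reader might infer that breaching criterion 4 or 7 removes a participant from the analysis.** The article does not say so. Section 2.5 speaks of ending participation, not of discarding data, and it describes efforts to keep people in follow-up. The Discussion lists sessions completed and medication timing as possible covariates, which suggests that such variation is to be accounted for. The defect is that these sections are not reconciled with intention-to-treat.

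**A reader might also infer wholesale deletion if every outcome in Table 1, at every visit, entered one MANOVA.** Section 2.4 does not say which outcomes enter together, and missing values in a visit-based trial tend to cluster by visit. No deletion rate of that kind can be derived from the article.

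**The loss of power is small.** This stands, and it is why the case rests on bias and on observed primary data going unused.

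**Conclusion.** The point holds in a limited form. The conditional intention-to-treat sentence is a defect on the face of the text. The three-visit MANOVA, without prior imputation, does not deliver intention-to-treat when drop-out is expected. On the half-seen-at-t1 assumption, about 9 of 88 participants would have the primary endpoint and still not be used, with a variance about 12% larger than necessary. Power of about 78% is close to target, on a correlation of 0.5 that the article does not state. The bias cannot be sized from the article; the shifts of up to 0.20 SD are illustrations.

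The documents do not support the stronger conclusion that randomised participants will be excluded by rule, either for incomplete data or for breaching the running criteria.

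**What to change.** 1. Replace the conditional sentence with an unconditional one: every randomised participant is analysed in the arm allocated, whatever their adherence.
2. Analyse gait speed with a likelihood-based mixed model for repeated measures (SPSS MIXED), with group, visit and their interaction, using every available visit. Name the group contrast at t1 as the primary test.
3. Reconcile sections 2.2.1 and 2.5 with this rule. State that breaches of criteria 4 or 7 after randomisation are recorded but do not remove a participant's data from the primary analysis, and add a sensitivity analysis that sets those data aside. What the rules on medication and outside therapy should be is a clinical matter, and this point does not touch it.

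The cost is wording and a change of procedure within the same software. No new data are needed, since the weekly calls already capture the relevant events. There are two small downsides. The primary estimate will include participants with changed medication or outside activity, which the sensitivity analysis addresses. The mixed model also still assumes that missing values are explained by the observed ones (missing at random), so reasons for loss should be reported by arm.

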**Figure 4 fig4:**
[figure not shown]
Biomechanical model and anatomical placement of motion capture markers. **(A)** Dynamometric platform used in the biomechanical gait assessment. **(B)** Instrumentation of Inertial Sensor Units measure, which will be attached by elastic straps provided by the manufacturer. Each sensor must be placed at the following zones: **(B.1)** Lumbar, located just below the spinosa of the lumbar vertebra 5. **(B.2)** Thighs, located at the lower limit of the upper third of the thigh, on its lateral surface. It is considered as the total measurement of the thigh from the greater trochanter to the interarticular line. **(B.3)** Legs, placed at the midpoint of the leg measured from the interarticular line to the medial malleolus. The sensor is positioned just medial to the tibial border. **(B.4)** Feet, positioned on the dorsum of the foot, four centimeters from the intersection of the inter-malleolar line, above a line projected toward the fourth toe.

The study’s primary outcome is Gait speed at the post-training time (primary time point), defined as the distance traveled by the body per unit of time (m/s). The Gait speed is an objective variable, easy to measure with or without instrumental equipment, and considered a relevant indicator of functional and health status (54, 55). In addition, the secondary outcomes of this trial are the Maximum gait speed (m/s) (56) and the Gait speed variability, calculated through the coefficient of variation ([standard deviation/mean] × 100) (57), which indicates how stable or repeatable the participants are when walking. These variables could be more sensible to gait impairments (58) and changes after treatment (57). On the other hand, the tertiary outcomes are those from the spatiotemporal, kinematics, and kinetics gait analysis, in addition to the scores of the scales and questionnaires proposed in Table 1.

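### The declared primary comparison, gait speed at t1, is not the primary test: it is reachable only post hoc, after an omnibus Group x Time MANOVA, and baseline gait speed and H&Y stratum are not covariates

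*Protocol article*

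**What the plan says.** Section 2.2.3 is specific: "The study’s primary outcome is Gait speed at the post-training time (primary time point"). Maximum gait speed and gait speed variability are secondary. Everything else in Table 1 is tertiary.

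Section 2.4 gives one efficacy analysis: "A two-factor mixed Multivariate Analysis of Variance (MANOVA) will be conducted to analyze the factors effects on the outcomes", taken at t0, t1 and t2. Its factors are Time ("The within-subject factor is *Time* with three categories (Baseline, Postintervention and Follow-up") and Group ("The between-subject factor is *Group* with two categories (GiG and GaG"). Specific comparisons come afterwards: "When significant effects are found, Bonferroni will be used for post-hoc comparisons". Among the assumption checks, "the correlation level between dependent variables will be observed with the Pearson correlation test", which implies that more than one dependent variable enters a model. The section does not say which outcomes these are. It gives gait speed no model of its own and lists no covariate.

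Two other places bear on the point. Section 2.3 stratifies randomisation by H&Y stage. The Discussion says that disease severity, sessions completed, medication timing, sex and daily activities should be taken into account as possible covariates. It does not name baseline gait speed, and section 2.4 takes up none of the list.

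**The concern.** A primary endpoint of one variable at one visit calls for one named test of that difference. None of the omnibus effects in section 2.4 (Group, Time, Group x Time) is the GiG minus GaG difference in gait speed at t1. The interaction comes closest, but it pools t1 with t2, and in a multivariate model it also pools gait speed with other outcomes. The declared comparison is then a follow-up that the wording permits only after a significant omnibus result, and which omnibus effect must be significant is left open.

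Two things are at stake. First, the confirmatory conclusion is not tied to a test: a clear gait-speed difference at t1 could go formally untested, or the report could rest on a different effect. Second, precision is lost if the t1 comparison is made without baseline gait speed, which is measured in every participant.

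**Working it through.** **Inputs from the protocol.** Section 2.2.4: f = 0.15, power 80%, alpha 5%, 2 groups x 3 times, total N = 74 (37 per arm at 1:1). Sections 2.2.3 and 2.4: endpoint and analysis as above.

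**Assumptions, not in the protocol.** Equal within-person correlation rho between visits (0.5 unless stated), sphericity, and no group difference at baseline.

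**1. Reproduce N = 74.** For the Group x Time interaction of a single outcome, lambda = f² x N x m / (1 − rho) = 0.0225 x 74 x 3 / 0.5 = 9.99, with 2 and 144 df. Power is 0.806, and 74 is the smallest even N that reaches 80%. A between-groups main effect would need 236. The stated size therefore fits the univariate interaction at rho = 0.5. That is neither a multivariate test nor the t1 comparison.

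**2. Difference at t1 implied by f = 0.15.** Take group differences of (0, d, d) at t0, t1, t2. Their deviations from the mean are (−2d/3, d/3, d/3). The interaction variance is (1/4) x (1/3) x (6d²/9) = d²/18, so f = d/√18 and d = 0.15 x √18 = 0.636 SD. The pattern (0, d, 0) gives the same d.

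**3. Direct test at t1, 37 per arm, two-sided 0.05.** The noncentrality is d x √(37/2) unadjusted. It is divided by √(1 − rho²) when baseline is a covariate.

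| Test of gait speed at t1 | Noncentrality | Power |
|---|---|---|
| Unadjusted | 2.74 | 0.77 |
| Baseline ANCOVA, rho 0.5 | 3.16 | 0.88 |
| Baseline ANCOVA, rho 0.7 | 3.83 | 0.97 |
| Baseline ANCOVA, rho 0.8 | 4.56 | 0.99 |

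**4. Gated route, one outcome.** In 20,000 simulated trials (rho 0.5), a significant interaction followed by a significant unadjusted t1 difference occurred in 0.64 (effect kept at t2) to 0.68 (effect at t1 only). With Bonferroni over the three visits the figures are 0.52 to 0.56. In the same simulations baseline ANCOVA had 0.87. Against the direct unadjusted test (0.77), the gate alone costs 0.09 to 0.13. The baseline covariate is worth a further 0.11.

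**5. Multivariate gate.** With p outcomes there are 2p time contrasts. The test is Hotelling's T² with 2p and 74 − 2p − 1 df and lambda = (74/4) x D². If only gait speed responds, D² = (d²/0.75) x k. Here k = [1 + (p − 2)r] / [(1 − r)(1 + (p − 1)r)], and r is the common correlation between outcomes. For p = 1, D² = 0.54, lambda = 9.99 and power is 0.80.

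| Outcomes in the model | Between-outcome r | k | Power of the gate |
|---|---|---|---|
| 3 | 0 | 1.00 | 0.60 |
| 3 | 0.4 | 1.30 | 0.73 |
| 3 | 0.6 | 1.82 | 0.88 |
| 3 | 0.7 | 2.36 | 0.96 |
| 26 | 0 | 1.00 | 0.11 |
| 26 | 0.8 | 4.81 | 0.52 |

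Three stands for the speed outcomes. Twenty-six is the count of repeatedly measured rows in Table 1 (8 clinical, 9 platform, 9 inertial-sensor). With three outcomes the gate is weaker than the univariate test at low correlation and stronger at high correlation.

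**The case against.** The best defence is that section 2.4 provides post-hoc comparisons, so the t1 difference can be reached. The interaction also uses baseline, because it compares change between arms, and it is a valid analysis. Both statements are correct. A reader might infer that the primary endpoint is never tested or that baseline is ignored, and the text supports neither. What stands is that the comparison is conditional and not named as primary, and that baseline is not a covariate. The covariate part concerns precision, not validity.

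A reader might also infer one joint model of all 26 rows, with a collapse in power or a near-singular covariance matrix. The protocol does not say that. It names no outcome set, its sample size fits a single outcome, and Mauchly's test suits outcomes taken singly. Forces in newtons and in percent of weight are not exact functions of each other across participants of different weight, and a multicollinearity check is planned. Dilution is not a general result either, as step 5 shows.

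Finally, a reader might fear that a Time effect, likely in both arms, would be presented as benefit of imagery. Section 2.4 does not restrict which effect opens the comparisons, but nothing says a Time effect would be read that way, and the stated hypothesis is a between-group one.

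Which outcomes are modelled together may fairly be left to a fuller plan. The mismatch is different: the article states an analysis, and that analysis does not have the declared endpoint as its test.

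**Conclusion.** The point holds in this form: the protocol declares one comparison as primary, and its only stated efficacy analysis makes that comparison a conditional follow-up, without baseline gait speed or the H&Y stratum as covariates. At 0.636 SD, 74 analysed and rho = 0.5, power for the declared comparison is about 0.64 to 0.68 through a one-outcome interaction gate, 0.77 by a direct unadjusted test and 0.88 with baseline as covariate. The first range assumes that the post-hoc comparison at t1 is unadjusted, which section 2.4 does not specify. The values at rho 0.7 and 0.8 keep d at 0.636, although N = 74 itself reproduces only near rho = 0.5. The size and direction of any further effect from a multivariate gate cannot be fixed from the document, so the conclusion does not rest on it.

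**What to change.** In section 2.4, name one primary test: the GiG minus GaG difference in gait speed at t1, from a model of gait speed alone with baseline gait speed and H&Y stratum as covariates (ANCOVA, or the t1 contrast of a mixed model for repeated measures). Test it two-sided at 0.05, report the 95% confidence interval, and do not make it conditional on any omnibus result. Analyse maximum gait speed and gait speed variability the same way. Keep the MANOVA, if wanted, as supportive or exploratory, and list the outcomes that enter it.

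Restate the sample size in section 2.2.4 for this test, with the assumed correlation. At 0.636 SD and rho = 0.5, ANCOVA needs 31 per arm for 80% power (40 per arm at correlation 0), so 37 analysed per arm is enough on the protocol's own effect size.

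The cost is analysis wording. No new data are needed, and SPSS fits either model. It should be settled before anyone sees outcome data by group.
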